## Methods/design

### Study design

The study will be a randomized, double-blind, sham-controlled clinical trial, which will include patients assigned to active taVNS and sham taVNS groups and healthy subjects assigned to a healthy control group (HC). The study timeline of events is listed in **Figure 1**. For included patients, this study consisted of three basic phases: (a) a one-week baseline; (b) a consecutive 12-week treatment period without weekend interruption (Week 1 - Week 12, W1-W12); and (c) a follow-up period of 12 weeks (Week 13 – Week 24, W13 - W24). After enrollment, an interview will be used to acquire general patient information, including age, gender, duration of HFA, family history, and results of the clinical assessment tools during the baseline. Following the baseline period, patients will be assigned to one of the two treatment groups randomly to receive active taVNS or sham taVNS treatment using a random number table, which will be generated by SPSS 25.0 before enrollment of the first patient. During the follow-up period, patients will be evaluated with clinical assessment tools as well as structural and functional imaging scans.

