#### Sample size estimation

Power Analysis and Sample Size Software version 15.0 (PASS, NCSS Statistical Software, Kaysville, UT, USA) was used to determine the study’s sample size. An alpha of 0.05 and a power of 0.9 are used in the study. Based on preliminary trial results, the Clancy Autism Behavioral Scale (CABS) score indicates a curative effect, so the mean and standard deviation of the paired differences are 5 and 8, respectively (15). The PASS software calculation resulted in a minimum requirement of 34 participants per group, accounting for an estimated 20% dropout rate. Considering a 15% rate of invalid MRI data based on previous experience, a minimum of 40 subjects will be recruited per group. Therefore, 40 patients will be enrolled in each group, totaling 80 patients for the study.

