### Statistical analysis

Basic analyses will be conducted using SPSS 25.0 software. At baseline, independent samples t-tests will be used to determine if there is no statistical difference between the two intervention groups; paired samples t-tests will then be used to examine the differences between mean scores before and after the taVNS intervention to determine the effectiveness of the treatment. Additionally, for the imaging study, we will use two-sample t-tests to compare brain network parameters between the HC and sham groups, as well as paired-sample t-tests to determine brain network parameters between the sham and active groups. Based on age and gender as covariates, a two-sample t-test will be used to compare the small-world properties and global parameters of the anatomical network between the HC group and the sham group. The level of significance for all statistical tests is set at p< 0.05. A Bonferroni correction will be performed on the t-tests utilized to examine group differences in behavioral and brain measurements, to account for multiple comparisons.

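### Clinical effectiveness is decided by before/after paired t-tests, and no active-versus-sham test of a clinical score is defined after baseline

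*Protocol article*

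**What the plan says.** All references are to the protocol article.

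- **Study design:** "The study will be a randomized, double-blind, sham-controlled clinical trial". The first objective, given at the end of the Introduction, is the therapeutic effect of taVNS in HFA.
- **Statistical analysis, clinical scores, between arms:** "At baseline, independent samples t-tests will be used to determine if there is no statistical difference between the two intervention groups". This is the only active-versus-sham comparison of clinical scores that the section defines.
- **Statistical analysis, clinical scores, effectiveness:** "paired samples t-tests will then be used to examine the differences between mean scores before and after the taVNS intervention". The same sentence gives this as the way to judge whether taVNS works.
- **Statistical analysis, imaging:** the arms are compared after all, by "paired-sample t-tests to determine brain network parameters between the sham and active groups". The two arms contain different children, so a paired test does not fit.
- **Statistical analysis, multiplicity:** "A Bonferroni correction will be performed on the t-tests utilized to examine group differences in behavioral and brain measurements". No arms and no visit are named.
- **Sample size estimation:** "An alpha of 0.05 and a power of 0.9 are used in the study". The inputs are a mean of 5 and an SD of 8 for paired CABS differences. They lead to 34 per group allowing for 20% dropout, and 40 per group allowing for 15% invalid MRI data.

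**The concern.** A change from baseline in treated children is the sum of the taVNS effect and everything else that moves the score: placebo response, maturation over 12 to 24 weeks, regression to the mean, and the effect of repeated rating. The sham arm is there to remove those components, and only a between-arm comparison does so. Here they are plausible, since CABS is parent-reported and the stimulation is carried out by patients and caregivers themselves.

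Running the paired test in each arm does not repair this. A significant result in one arm and a non-significant one in the other is not a test of the difference between them.

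The baseline t-test is a lesser matter. After randomisation any baseline difference is due to chance, and a non-significant result with 40 per arm does not show balance.

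At stake is the main clinical claim: followed as written, the analysis could declare taVNS effective when it does no better than sham.

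**Working it through.** **1. Reproduce the plan's sample size.** Inputs from Sample size estimation: mean paired difference 5, SD 8, alpha 0.05 (sidedness not stated; two-sided assumed), power 0.90.

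- One-sample (paired) normal formula: n = (SD × (z₀.₉₇₅ + z₀.₉₀) / mean)² = (8 × 3.2415 / 5)² = 26.9, so 27.
- Dropout: 27 / 0.80 = 33.75, so 34.
- Invalid MRI: 34 / 0.85 = 40.

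Both stated figures are reproduced. A two-sample comparison with the same inputs needs 54 per arm, or 68 after dropout, and so does not give 34. The size rests on the same before/after contrast as the efficacy test.

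**2. How often the before/after test is significant when taVNS adds nothing.** Let both arms improve by c points on average, with SD of change 8 and n = 40 × 0.80 = 32 completers. The paired t statistic has 31 degrees of freedom, two-sided critical value 2.040 and noncentrality c√32/8. With p the probability of significance in one arm, independent arms give the pattern of active significant and sham not with probability p(1 − p).

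| Common improvement c (assumed) | Noncentrality | p, active arm | p(1 − p) |
|---|---|---|---|
| 0 | 0 | 5% | 5% |
| 2 | 1.41 | 28% | 20% |
| 3 | 2.12 | 54% | 25% |
| 5 | 3.54 | 93% | 7% |

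With all 40 evaluable, p is 34%, 64% and 97% for c = 2, 3 and 5. The documents give no sham response, so c is a range of assumptions. The value 5 is the plan's own before/after change.

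**3. Power of the between-arm comparison at the planned size.** Assume a true active-minus-sham difference in change of 5 and SD of change 8 in each arm. The documents give no between-arm difference. The noncentrality is (5/8)√(n/2).

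- 32 evaluable per arm: 2.50, power about 69%.
- 40 evaluable per arm: 2.80, power about 79%.
- For 90% power: 55 evaluable per arm.

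**4. What baseline adjustment recovers.** With equal variances at baseline and follow-up and correlation rho, the ANCOVA residual variance is (1 + rho)/2 times the variance of change. Rho is not in the documents, so two values are shown.

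| rho (assumed) | Residual SD | Power, 32 per arm | Evaluable per arm for 90% |
|---|---|---|---|
| 0.5 | 8√0.75 = 6.93 | 81% | 42 |
| 0.7 | 8√0.85 = 7.38 | 76% | 47 |

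If sham also improves, so that the difference is below 5, all these powers fall.

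**The case against.** The strongest reply is the Bonferroni sentence, which speaks of group differences in behavioural measures and suggests that some between-group behavioural t-tests are intended. It could equally mean the baseline comparison or a comparison with healthy controls. It corrects tests defined elsewhere, and no post-baseline active-versus-sham clinical test is defined elsewhere. It shows possible intent but supplies no test.

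A second reply is that this is a condensed article and the detail may sit in an analysis plan that is not shown. That would answer an omission. Here the article names a test and gives its purpose, and the sample size is built on the same contrast.

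Some stronger readings are tempting, but the text does not support them:

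- **Sham is never compared with active.** It is compared for brain-network parameters, though with a test that does not fit.
- **W4, W16 and W24 are ignored.** The section names no visit, so paired tests at several visits are not excluded.
- **Children without both scores are dropped.** Missing-data handling may be set out elsewhere and is not criticised here.
- **The trial cannot meet its first objective.** Both arms are randomised and assessed by blinded observers at five time points, so the data would support a proper comparison. It is the stated analysis that fails.

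**Conclusion.** The point holds, and it must be fixed before analysis. For the clinical scores, the test that decides effectiveness is a within-patient one, and nothing in the article replaces it with a randomised comparison after baseline.

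The size of the error depends on how much children improve without an active effect. The nominal 5% holds only if there is no such improvement, and an improvement of 3 points already makes a positive finding more likely than not. The pattern of active significant and sham not is most frequent near that value, at about one trial in four, and becomes rarer again at larger improvements because sham is then usually significant too. These figures rest on SD 8, 32 completers per arm, two-sided 0.05 and the assumed common improvements.

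The stated 90% power belongs to the before/after test and cannot be quoted for the comparison that the design calls for.

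**What to change.** **Analysis text.** Replace the effectiveness sentence with wording along these lines: the primary efficacy analysis is the active-minus-sham difference in the primary clinical score at a named post-treatment visit, in all randomised patients, adjusted for the baseline score and reported with a 95% CI. The sponsor has to name the score and the visit. CABS is the score used for sizing and W12 is the end of treatment, but the article designates neither as primary. ANCOVA at the chosen visit or a mixed model over the visits would serve. With dropout the two need not give the same estimate, so one should be specified.

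**Related text.** Make within-arm changes descriptive. Replace the baseline significance tests with a descriptive table. Change the sham-versus-active imaging comparison to a test for independent groups. State which group comparisons the Bonferroni correction covers.

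**Cost.** The analysis change is wording only, with no new visits or measurements. The sample-size section must be restated for the between-arm contrast, with its assumed difference, SD and correlation. At 40 per arm the sponsor then either accepts and reports the lower power or recruits more. On the assumptions above, 90% power needs 42 to 55 evaluable children per arm, or 53 to 69 randomised per arm after 20% dropout (42/0.80 = 52.5; 55/0.80 = 68.75), before any allowance for invalid MRI data.

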**Methods and design:**

We planned to employ a randomized, double-blind experimental design, including 40 children receiving sham stimulation and 40 children receiving real stimulation. We will assess clinical scales and perform functional imaging examinations before and after the stimulation. Additionally, we will include age- and gender-matched healthy children as controls and conduct functional imaging examinations. We plan first to observe the therapeutic effects of taVNS. Furthermore, we will observe the impact of taVNS stimulation on the brain network.

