### Participants

#### Recruitment of participants

The Beijing Children’s Hospital Department of Psychiatry will recruit participants with HFA diagnoses from clinical practice, and a clinical multidisciplinary team involving two experienced psychiatrists will diagnose patients according to the DSM-5 diagnostic criteria. The inclusion criteria are as follows:

the age range is between 6-12 years old.Wechsler intelligence test IQ of at least 80 for Chinese children.ability and willingness to cooperate with relevant assessments and tests.right-handedness.

The exclusion criteria include:

seizure disorder or other neurological diseases (including brain tumors and craniocerebral trauma).concomitant with other mental disorders, except for attention deficit hyperactivity disorder (ADHD) and obsessive-compulsive disorder (OCD).claustrophobia.impulsivity or aggression.presence of metal products in the body.

Discontinuation and withdrawal criteria:

sudden acute illness who are unable to progress to the next phase in the study.poor adherence, and biased results will be regarded as withdrawing from the study.other uncontrollable factors or self-withdrawal from the study.

In this study, recruitment is set to occur over a period of one and a half years (from August 2023 to December 2024). Beijing primary schools will be recruited to provide healthy controls meeting the following inclusion criteria:

The age range is between 6-12 years old.IQ of at least 80.right-handedness.

Exclusion criteria include:

diagnosis of neurological or mental disorders.claustrophobia.presence of metal products in the body.

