#### MR preprocessing

Each participant’s rs-fMRI data will be preprocessed using Statistical Parametric Mapping software (SPM12) and a powerful toolbox called Data Processing & Analysis of Brain Imaging (DPABIV7.0). The following specific steps will be performed for each subject: converting the DICOM to NIFTI format, removing the first ten time points to exclude the effects of subject maladaptation and magnetic field inhomogeneity at the beginning of the scan, and leaving the remaining time points for further spatial and temporal alignment and head rotation correction. If the subject’s head movement is >2 mm in the translation range or >2 ° in rotation, the subject’s data should be excluded. Additionally, time and spatial normalization procedures will be conducted. The images will be aligned to the Montreal Neurological Institute (MNI) space, with each voxel measuring 3 × 3 × 3 mm³. Nuisance covariates, including the Friston 24 parameter model, as well as signals from cerebrospinal fluid and white matter, will be removed through regression analysis to correct the realigned data. A 4 mm full width at half-maximum isotropic Gaussian kernel was utilized for spatial smoothing, while linear signals were eliminated. Furthermore, a temporal band-pass filter will be applied, restricting the frequency range to 0.01–0.08 Hz (47). The diffusion tensor imaging data preprocessing will be conducted using the open-source software Pipeline for analyzing brain diffusion images (PANDA), which also allows for the construction of brain networks and can be downloaded at http://www.nitrc.org/projects/panda/. The preprocessing typically involves several key steps. First, the 3D T1 structural image will be co-registered with the b0 image to eliminate the effects of eddy current distortions and motion artifact; next, extraction of brain tissue from corrected data, removal of scalp and other non-brain tissue structures; the diffusion space will be subsequently aligned with the T1 template, utilizing the MNI space as a reference. Thus, the diffusion space will be mapped to the MNI space, facilitating the reconstruction of fibers connecting each pair of brain regions within this space. The whole-brain fibers will be constructed using a fiber assignment algorithm based on continuous tracking. The interregional connection density will be quantified as the fractional anisotropy (FA) value. Based on our experience, fiber tracking will cease at voxels where FA < 0.2 or when the angle between two consecutive voxel’s eigenvectors exceeds 35° (48).

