
### Network construction and analysis

#### Functional network

A brain network is composed of nodes and edges. We will also use the AAL template to construct the functional network to assign each brain region without the cerebellum as an anatomical region of interest (ROI). The ROIs will then be designated as nodes within the functional network, allowing us to extract the average time series for each node. An edge in a functional network is thought to be a functional connection between two brain areas. By calculating the Pearson correlation coefficient between the time series of each pair of ROI regions, we will obtain the functional connectivity matrix of each subject’s brain. It allows for a more complete understanding of the network organization since it contains additional information about the strength of functional connectivity on a continuous scale (49).

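### The functional-network comparison of healthy controls with the sham group has no group-level head-motion term, so any residual motion difference between these non-randomised groups would be confounded with the network difference

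*Protocol article*

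**What the plan says.** The Statistical analysis section gives one general rule for the control contrast: "we will use two-sample t-tests to compare brain network parameters between the HC and sham groups". A second sentence adds covariates, but for the anatomical network only: "Based on age and gender as covariates, a two-sample t-test will be used to compare the small-world properties and global parameters". No other group-level covariate appears in the article.

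Motion in the resting-state fMRI data is dealt with earlier, under MR preprocessing, by realignment and two further steps:
- A subject's data are excluded if "head movement is >2 mm in the translation range or >2 ° in rotation".
- Within each remaining scan, "Nuisance covariates, including the Friston 24 parameter model, as well as signals from cerebrospinal fluid and white matter, will be removed through regression analysis".

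The functional network is then built from the processed series: "By calculating the Pearson correlation coefficient between the time series of each pair of ROI regions".

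On comparability of the groups, the abstract says "we will include age- and gender-matched healthy children as controls". The patient exclusion criteria remove children "concomitant with other mental disorders, except for attention deficit hyperactivity disorder (ADHD) and obsessive-compulsive disorder (OCD"), whereas controls may have no mental or neurological diagnosis.

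**The concern.** The exclusion limit and the regression both act on one scan at a time. Neither makes the two groups alike in whatever motion artefact remains afterwards. In a randomised comparison, allocation would balance that remainder on average. Healthy controls against sham patients is not a randomised comparison, and its matching covers age and gender only.

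The populations differ in a way that could bear on how still a child lies in a scanner: one has high-functioning autism with ADHD permitted, the other has no diagnosis. If residual motion differs and is correlated with the network metrics, a plain t-test attributes that part of the difference to disease.

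This matters because the closing paragraph of the Introduction makes brain-network remodelling the second of two primary objectives. It includes differences between patients and controls from both structural and functional perspectives, and its hypothesis is framed in terms of network efficiency. Efficiency, clustering and path length in the functional network all derive from the same correlation matrix.

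**Working it through.** **1. The plan's own figure.** The Sample size estimation section states that "An alpha of 0.05 and a power of 0.9 are used in the study", with a paired-difference mean of 5 and SD of 8. The normal approximation gives n = ((1.960 + 1.282) × 8/5)² = 26.9, so 27. Allowing for 20% dropout, 27/0.80 = 33.75, so 34. Allowing for 15% invalid MRI data, 34/0.85 = 40. Both stated numbers reproduce, and this point does not change them.

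**2. Inputs for the motion check.**
- Usable scans: 40 × 0.85 = 34 per group. The size of the control group is not stated; 40 recruited is assumed.
- Two-sided 5% test (sidedness is not stated; two-sided reproduces the plan's figure).
- D, the between-group difference in residual motion in SD units, and r, the correlation of residual motion with the network metric. Neither is in the documents. Both are assumed, over D = 0.2 to 0.8 and r = 0.1 to 0.5.

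**3. Model.** With no true group difference, metric = r × motion + √(1 − r²) × noise. The spurious standardised difference is then r × D, and the t statistic has noncentrality r × D × √(n/2) with 2n − 2 = 66 degrees of freedom. At n = 34, √(34/2) = 4.123. The critical value is 1.997 at 0.05. Taking the five small-world and two global metrics in Network analysis as one Bonferroni family (an assumption), the per-test level is 0.05/7 = 0.0071 and the critical value is 2.777.

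| D (SD) | r | r × D | Noncentrality | False-positive rate at 0.05 | Per-test rate at 0.05/7 |
|---|---|---|---|---|---|
| 0.2 | 0.1 | 0.02 | 0.082 | 5.1% | 0.7% |
| 0.5 | 0.1 | 0.05 | 0.206 | 5.5% | 0.8% |
| 0.5 | 0.3 | 0.15 | 0.618 | 9.4% | 1.9% |
| 0.8 | 0.3 | 0.24 | 0.990 | 16.4% | 4.2% |
| 0.5 | 0.5 | 0.25 | 1.031 | 17.4% | 4.6% |
| 0.8 | 0.5 | 0.40 | 1.649 | 36.9% | 13.9% |

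**4. What Bonferroni does.** It lowers every per-test rate, but the shift r × D is unchanged. Relative to nominal, the D = 0.5, r = 0.3 row goes from 9.4/5 = 1.9 times to 1.9/0.71 = 2.6 times. The D = 0.8, r = 0.5 row goes from 7.4 times to 13.9/0.71, about 19 times.

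**5. Effect of a motion covariate.** In 20,000 simulated trials with 34 per group, the unadjusted test rejected in 9.0% (D = 0.5, r = 0.3) and 37.4% (D = 0.8, r = 0.5). A linear model with motion as covariate rejected in 4.7% and 4.5%. In this simulation the motion effect is linear and motion is measured without error, so the full return to nominal is partly built in.

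**The case against.** The strongest case against has four parts.

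- **Condensed article.** A covariate list may be left to an imaging analysis plan. This stands in part and lowers the weight of the point. But the section does more than stay silent: it names the test, and it names covariates for one control contrast and not for the other. As written, the functional contrast is a t-test, which cannot carry a covariate.
- **Motion is already handled.** Realignment, exclusion, the 24-parameter regression, tissue-signal regression and band-pass filtering are all planned. This stands: only the remainder after those steps is at issue. They do not balance that remainder between groups.
- **No evidence that motion differs.** The documents report no motion by group and no motion-metric correlation. The Recruitment section also requires patients to be able and willing to cooperate with tests and excludes impulsivity or aggression, which may narrow any gap. This stands, and is why the range must start at no effect.
- **Limited consequence.** The contrast is non-randomised and mechanistic. This stands for efficacy, though the contrast serves a stated primary objective.

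A reader might infer that motion is uncontrolled in this trial, or that a patient-control difference in efficiency would be a motion artefact. The documents support neither. A reader might also extend the point to all patients, but the planned control contrast is with the sham group only.

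**Conclusion.** The point holds in a limited form. Gross movers are excluded and motion is regressed within subject, but the functional contrast of healthy controls with sham has no group-level motion term and no matching on motion. A residual difference, if there is one, would be confounded with the network difference.

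Its size cannot be derived from the documents. On assumed inputs it ranges from negligible (about 5% false positives at D = 0.2, r = 0.1) through 9% (D = 0.5, r = 0.3) to 37% (D = 0.8, r = 0.5), before Bonferroni. The upper end requires a large motion difference and a strong correlation that both survive preprocessing. The case for acting rests on the low cost of the remedy and on the contrast's place in a primary objective, not on any demonstrated inflation.

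**What to change.** In the Statistical analysis section, replace the plain t-test for the functional-network contrast of healthy controls with sham by a linear model containing group, age, gender and each scan's mean framewise displacement, calculated from the realignment parameters that preprocessing already produces. Report mean motion by group. Show the group difference without the motion term alongside the adjusted one, so that readers can see how much depends on it. Including age and gender also brings the functional contrast into line with the anatomical one.

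The cost is three degrees of freedom relative to the plain t-test (66 becomes 63 at 34 per group), one of them for motion. No new data are needed and the sample size is unchanged. If motion is part of the phenotype, the adjusted difference may be mildly over-corrected, which is the reason for showing both results.

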Based on the aforementioned evidence, we designed our protocol with two primary objectives: First, it aims to examine the therapeutic effects of taVNS in individuals diagnosed with HFA; Second, it intends to investigate the process of brain network remodeling after taVNS using functional imaging techniques. We will use graph-theoretic analysis to compare the brain network characteristics of individuals with HFA before and after receiving taVNS. Additionally, we will examine the differences in these characteristics between patients with HFA and healthy controls, considering both structural and functional connectivity perspectives. Our hypothesis posits that taVNS has the potential to enhance the efficiency and flexibility of brain networks in HFA patients, leading to an improvement in their social cognitive abilities.

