**Figure 1 f1:**
[figure not shown]
A schematic representation of the study timeline of events.

The treatment condition assignment will remain undisclosed to patients and independent observers who perform clinical assessments and MRI scan technicians until the last interview. Only the technicians performing the taVNS procedure and the physician assigning the randomization without patient contact will be aware of the group information. No communication will be allowed between patients during any phase of the study to maintain blindness.

Patients will be evaluated using the clinical assessment tools at five time points (baseline; W4, the first month of treatment; W12, right after treatment; W16, short-term follow-up; W24, long-term follow-up) (**Table 1**). MRI scan will be acquired at three time points (baseline, W12, and W24). More details regarding the clinical procedures can be found in **Figure 2**; **Table 1**. Healthy subjects in the HC group will be evaluated with the same clinical tools and undergo an MRI scan only once. The clinical endpoints are assessed by blinded observers who are not involved. Furthermore, all dropouts will be documented and reported, specifying the reasons for their withdrawal.

**Table 1 T1:** Measurements at each time point.

Measurements/time point	Recruitment	Baseline	4 weeks	12 weeks	16 weeks	24 weeks
Inclusion/exclusion criteria	√	N/A	N/A	N/A	N/A	N/A
Behavioral Checklist for Children with High-Functioning Autism/Asperger’s Disorder	N/A	√	√	√	√	√
ABC	N/A	√	√	√	√	√
CABS	N/A	√	√	√	√	√
SRS	N/A	√	√	√	√	√
WISC	N/A	√	√	√	√	√
MRI scanning	N/A	√	N/A	√	√	√

√, need to be finished; ABC, Autism Behavior Checklist; CABS, Clancy Autism Behavioral Scale; SRS, Social Responsiveness Scale; WISC, Wechsler Intelligence Scale. N/A, Not applicable.

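### Healthy controls are compared with the sham arm only, at an unstated time point, although the aim concerns all HFA patients and every one of them has a pre-randomisation baseline scan

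*Protocol article*

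**What the plan says.** The Introduction of the protocol article states the aim for the patient population as a whole: "we will examine the differences in these characteristics between patients with HFA and healthy controls", from both the structural and the functional side.

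The Statistical analysis section plans a narrower contrast and names it twice. The general imaging sentence gives "two-sample t-tests to compare brain network parameters between the HC and sham groups". A later sentence reads "Based on age and gender as covariates, a two-sample t-test will be used to compare the small-world properties and global parameters" and continues "of the anatomical network between the HC group and the sham group". Neither sentence gives a time point. No comparison of controls with all HFA patients, or with the active arm, is described.

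The Study design section sets the order of events: "Following the baseline period, patients will be assigned to one of the two treatment groups randomly". Patients have MRI at baseline and again at weeks 12 and 24 (Table 1 also ticks week 16), whereas healthy controls "undergo an MRI scan only once". The Sample size estimation section says "40 patients will be enrolled in each group, totaling 80 patients for the study". No number of healthy controls is given; the Abstract says only that they will be matched on age and gender.

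**The concern.** The planned contrast does not match the stated aim. At baseline nobody has been stimulated, so the two arms are exchangeable samples of untreated HFA children. Nothing in the design calls for leaving one arm out of the comparison with healthy children.

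The missing time point matters because the two readings differ in kind. A baseline comparison costs precision only. A week 12 or week 24 comparison sets children who have had 12 weeks of sham stimulation, and are 12 to 24 weeks further on, against controls scanned once. Diagnosis is then no longer the only difference between the groups.

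The covariate wording is a second, smaller problem. A two-sample t-test has no place for age and gender; adjustment needs a linear model. The covariates are also attached only to the small-world and global parameters of the anatomical network. The general sentence, which is the only one that can cover the functional network, names none.

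At stake are the precision and interpretation of the patient-versus-control part of the imaging aim. The efficacy comparison is not affected.

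**Working it through.** **The plan's own figure.** The sample size comes from a paired CABS change with mean 5, SD 8, alpha 0.05 and power 0.9. Taking alpha as two-sided and using the normal approximation:

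- n = (8 × (1.960 + 1.282) / 5)² = 26.9, so 27
- 20% dropout: 27 / 0.80 = 33.75, so 34
- 15% invalid MRI: 34 / 0.85 = 40

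The stated 34 and 40 per group reproduce. They rest on a within-patient clinical change, so they do not size the comparison with healthy controls.

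**Inputs for the control contrast.**

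- HFA baseline scans: 40 with sham only, 80 with both arms (Sample size estimation; Study design).
- Number of controls, n: not stated. Assumed 40, range 20 to 80.
- Effect: not stated. Assumed 0.5 SD for illustration, with 0.3 and 0.8 SD as the range.
- Equal SD in both groups; two-sided alpha 0.05 without correction.

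**Variance.** The variance of a difference in means, in units of SD², is 1/n + 1/m, where m is the number of HFA scans. The ratio of pooled to sham-only is (1/n + 1/80) / (1/n + 1/40).

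| Controls n | Sham only (m = 40) | Pooled (m = 80) | Ratio | Reduction |
|---|---|---|---|---|
| 20 | 0.0750 | 0.0625 | 0.833 | 17% |
| 40 | 0.0500 | 0.0375 | 0.750 | 25% |
| 80 | 0.0375 | 0.0250 | 0.667 | 33% |

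With 40 controls the standard error falls from √0.0500 = 0.224 SD to √0.0375 = 0.194 SD.

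**Power.** Two-sample t-test, noncentral t, noncentrality d / √(1/n + 1/m), 40 controls:

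| Assumed effect | Sham only | Pooled |
|---|---|---|
| 0.3 SD | 0.26 | 0.34 |
| 0.5 SD | 0.60 | 0.73 |
| 0.8 SD | 0.94 | 0.98 |

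At 0.5 SD the figures are 0.43 and 0.51 with 20 controls, and 0.73 and 0.88 with 80. If the protocol's 15% invalid-MRI rate applies to every group (34 controls; 34 against 68 HFA scans), they are 0.53 and 0.65.

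**Multiplicity.** The plan applies a Bonferroni correction, so these levels are too high for the analysis as planned. If the correction spans the five small-world and two global measures in the Network analysis section (an assumption; alpha 0.05 / 7), power at 0.5 SD with 40 controls is 0.31 with sham only and 0.44 pooled.

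**The case against.** The strongest reply is that the sham arm is a random half of the HFA sample. A baseline comparison with controls therefore estimates the right difference without bias. That stands. A reader might infer that the stated question is not answered at all; the text does not support this, because the time point is open and the baseline reading answers the question, only less precisely.

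A reader might also infer that the active-arm scans are thrown away. They are left out of this contrast only; the before-and-after and active-versus-sham network comparisons can still use them.

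On the covariates, a t-test with covariates may be loose wording for the test of the group term in a linear model, which is the analysis proposed below. That is a fair reading for the anatomical network, so it would be wrong to claim that adjustment will certainly be absent there. It does not help the functional network, for which no covariates are named. Matching controls on age and gender deals with part of the age concern by design. It does not replace the adjustment, which the protocol itself plans.

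Finally, the power figures depend on an effect size and a control number that the document does not give, and the gain is small if the effect is large. That stands too. The variance ratio depends only on the control number and is the safer summary.

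**Conclusion.** The concern holds in this form. The control contrast is restricted to the sham arm without a stated reason or time point, while the aim concerns HFA patients in general and 80 pre-randomisation scans are planned. On the baseline reading the cost is precision: pooling would cut the variance by 25% with 40 controls, and by 17% to 33% over 20 to 80. On a week 12 or week 24 reading, sham exposure and time are added to the contrast. The covariate model is misnamed and stated for one network only.

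The power gain from 0.60 to 0.73 is illustrative. It assumes 0.5 SD, 40 controls, all scans usable and no multiplicity correction. The point does not bear on the efficacy analysis, and using half the sample creates no bias by itself. It is still worth correcting, because the gain needs no extra scans.

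**What to change.** Replace the two sentences on controls versus sham in the Statistical analysis section with wording such as: Baseline network parameters of all HFA patients, both arms pooled, will be compared with those of healthy controls by linear regression with terms for group, age and sex, for the functional and the structural networks.

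State the comparison of active with sham as a separate contrast. If a comparison of controls with sham patients at week 12 or 24 is also wanted, name its time point and purpose and keep it apart from the baseline comparison. State the planned number of healthy controls so that the precision of the contrast can be judged.

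The cost is a change of wording. All the HFA scans needed are already in the schedule.
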